### Variables

The primary outcome will be the reduction in pain intensity, according to the visual analogue scale (iVAS), at 2 weeks after the start of treatment. The secondary outcomes will be functional status with respect to LBPGP (according to the Roland-Morris disability questionnaire) and health-related quality of life (SF12) at 2 weeks after the start of treatment, iVAS score at 12 and 48 weeks postpartum, presence of temporary occupational incapacity, reduction in the consumption of analgesic medication at 2 weeks, and presence of pain at 12 and 48 weeks postpartum.

The obstetric data, based on the patient’s health record, will consist of gestational age (weeks), number of previous pregnancies, number of children, previous caesarean sections, and whether epidural anaesthesia was required. The personal data compiled by the midwives participating in the study will be patient’s age (years), weight before pregnancy and present weight (kg), height (cm), body mass index before pregnancy (calculated as weight/height^2^), educational level (none, primary education, secondary education, high school, university), and employment status (employed, non-employed, type of work and, where appropriate, the reasons for not working). In addition, any previous pregnancy-related LBPGP will be recorded. If the patient is temporarily unable to work, the days elapsed since this condition began will be noted, and its follow-up at T2, T3, and T4. The data form will also record the consumption of healthcare resources since the beginning of the LBPGP (number of times treated by the family doctor, number of times emergency treatment needed at the health centre or hospital, number of visits to a medical specialist, private doctor, company doctor, or non-conventional healthcare professional).

In addition, data will be recorded for pain intensity, location (lower back, posterior pelvis or both, and whether pain is radiating to the leg), onset, and frequency of pain (occasional days, nearly every day, every day). Pain intensity will be measured by a visual analogue scale (iVAS) at T0, T1, and T2, as well as at the follow-up assessments T3 and T4. There is ample evidence supporting the validity of the iVAS for pain intensity, and many studies have corroborated its construct validity [35] and reliability [36,37]. It is a simple and fast method to assess subjective pain intensity. The patient is asked to mark on a 100-mm scale from 0 (no pain) to 100 (worst pain imaginable) the intensity of back pain by day (iVASd) and night (iVASn). The primary outcome, the change in pain intensity (iVAS) at 2 weeks after the start of treatment (T2), will be determined from the maximum value of the daytime pain measurements (iVASd) or the night-time ones (iVASn) at 2 weeks after starting treatment. There is evidence that reductions of greater than 35 mm on this scale are associated with an improvement perceived by the patient [38].

The women taking part in the study will be asked to complete the Roland-Morris disability questionnaire to assess the level of disability provoked by LBPGP at T0 and at T2. This self-administered questionnaire has been validated for use in Spain [39] and consists of 24 questions or statements related to incapacity caused by LBP. Respondents are asked to award one point for each statement that corresponds to their current situation. Scoring is quick and easy: the total score awarded may range from 0 points (no incapacity caused by LBP) to 24 (maximum incapacity). Changes in health-related quality of life are valued according to the SF-12 v.2 self-administered questionnaire. This is a generic questionnaire, derived from SF-36, which has been validated for use in Spain [35]. Version 2 allows the researcher to calculate the respondent’s quality of life in eight domains (physical function, physical role, pain, general health, vitality, social function, emotional role, mental health) and two summary components (physical and mental). A version with six items, to enable the calculation of utilities, is currently being validated. In our study, this would enable a cost-effectiveness analysis to be conducted.

The presence of anxiety and/or depression will be screened and assessed at T0 and T2 by the Spanish version of the Goldberg Depression Inventory [40]. This consists of two scales, one for anxiety and one for depression, each with nine dichotomous items (yes/no answers). A separate score is given for each scale, with one point for each affirmative answer. In this Inventory, which may be applied by the researcher or be self-administered, the patient is asked whether in the last 2 weeks any of the symptoms referred to in the questions have occurred. Symptoms lasting less than 2 weeks or of only mild impact are not counted. The questionnaire can be applied even by non-medical staff, and no standardisation is required. Each of the subscales is divided into four initial screening items to determine whether a mental disorder is likely to be present, and a second group of five items will be asked only if positive responses are given to the screening questions (scores of ≥2 on the anxiety subscale and ≥1 on the depression subscale). Cut-off points are ≥4 for the anxiety scale and ≥2 for the depression scale. There is a clear improvement in the sensitivity of this Inventory with increasing severity of the psychopathology, with higher scores being obtained, which can provide a separate dimensional measure of the severity of each disorder. Raising the cut-off points to ≥5 and ≥3 improves the specificity and the discriminatory power of the scales, but slightly reduces their sensitivity (specificity 93%, sensitivity 74%).

At the end of treatment (T2), the patient’s perceived improvement will also be assessed. A 7-point Likert scale has been recommended to assess the perceived improvement of a patient with non-specific LBP [41], but opinions differ regarding the categories to be used; we opted for the suggestion made by Hudak and Wright [42]: How satisfied are you with the results of your recent treatment for low back pain and/or posterior pelvic pain? 1 = very satisfied, 2 = very satisfied, 3 = somewhat satisfied, 4 = indifferent (about equally satisfied and dissatisfied), 5 = somewhat dissatisfied, 6 = very dissatisfied, and 7 = extremely dissatisfied.

We will also evaluate the consumption of analgesic medication, whether or not prescribed by the patient’s doctor, both at the time of randomisation (T0) and at final assessment (T2), according to a 4-point Likert scale of 0–3: (0) = none, (1) = less than the usual dose, (2) = usual daily dose, and (3) = greater than the usual dose. We will also record the names of the medications taken and the daily dose in each case.

The Treatment Credibility Scale [43] will be used to evaluate patients’ expectations and the credibility of the treatments provided in the study. The original Borkovec and Nau scale [44] with four items will be applied, assessing the following questions on a continuous VAS of 0 to 10 (0 to 10, from totally disagree to totally agree): (1) = Are you confident that this treatment can alleviate your pain? (2) = Does it seem a logical treatment? (3) = Would you recommend this treatment to a friend or family member who was suffering the same problem? (4) = Do you think this treatment would be an option for treating other problems? Questions 1 and 2 will be assessed after the first treatment session, and questions 3 and 4, after 2 weeks.

After the treatment has concluded, the blinding of the patients’ allocation to one of the two auricular acupuncture groups (real or placebo) will be verified by the following dichotomous question: Do you think you were assigned to the real auricular acupuncture group or to the placebo group?

During the study, side effects and possible adverse reactions resulting from the treatment will be recorded.

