### Hypothesis and study goals

Our clinical hypothesis is that acupuncture applied via pressure needles inserted in the auricle (VAAc), associated with standard obstetric care (SOC), can reduce the pain experienced by pregnant women in the lower back and/or the posterior pelvic girdle, to a greater extent than is achieved by SOC alone in the field of primary health care. Additionally, the application of this technique improves patients’ functional status and health-related quality of life, and moderates the consumption of drugs used in conventional therapy, thus reducing the associated iatrogenic effects without provoking significant iatrogenesis in itself. Secondly, VAAc applied together with SOC has specific effects, achieving a greater reduction in the LBPGP suffered by pregnant women than that achieved with the application of pressure needles at non-specific pressure points (NSAAc) or with placebo needles at non-specific points (PAAc).

The main aim of this study is to evaluate the efficacy achieved in terms of reduction in pain intensity (0 to 100 mm visual analogue scale) at 2 weeks after starting treatment. Our secondary aims are: i) to evaluate the efficacy in terms of improved functional status with respect to LBPGP (according to the Roland-Morris disability questionnaire) at two weeks after starting treatment; ii) to evaluate the efficacy in terms of improved health-related quality of life (SF12) at two weeks after starting treatment; iii) to evaluate the efficacy in terms of improvement perceived by the patient with LBPGP at two weeks after starting treatment; iv) to evaluate the impact on temporary occupational incapacity of pregnant women with LBPGP; v) to evaluate the efficacy in terms of reduced consumption of analgesic medication at 2 weeks after starting treatment; vi) to evaluate the presence of LBPGP at 12 weeks postpartum; vii) to evaluate the presence of LBPGP at 48 weeks postpartum; and viii) to estimate the placebo effect and the specific and non-specific effects of VAAc, NSAAc, and PAAc.

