### Statistical analysis

A descriptive analysis will be performed to assess the comparability of the four groups with regard to baseline demographic information, prognostic variables, and the evaluation of credibility, using measures of central tendency and dispersion for the quantitative variables and frequency distributions for the qualitative ones.

To determine the primary study outcome (change in pain intensity at 2 weeks) and secondary outcomes (change at 2 weeks in functional status with respect to pain, quality of life, and improvement perceived by the patient), a crude analysis will be performed to compare the mean differences between baseline values and at 2 weeks, for the VAAc group and the SOC group, using the Student *t*-test for independent samples or the Mann-Whitney U test if the samples do not present a normal distribution (determined by the Shapiro-Wilk test). Subsequently, simple and multivariate linear regression analyses will be performed, using the same outcome variables, to adjust for unbalanced independent variables, including the treatment group in the first pass, and determining regression coefficients with the corresponding 95% confidence intervals and the coefficient of determination. The main analysis will be by intention-to-treat, but a per protocol analysis will also be performed.

To determine the secondary outcomes of presence of temporary occupational incapacity, reduction in the consumption of analgesic medication at 2 weeks, and presence of pain at 12 and 48 weeks postpartum, the VAAc and SOC groups will be compared, using the χ^2^ test with continuity correction or Fisher’s exact test when the expected values are below 5. Then, simple and multivariate logistic regression models will be obtained, with the same outcome variables, to adjust for unbalanced independent variables, including the treatment group in the first pass, and the relative risk will be determined, with 95% confidence intervals.

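### The item for aim iii (perceived improvement) asks about satisfaction with treatment results, and two of its seven codes carry the same label

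*Protocol article*

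**What the plan says.** The aims, under Hypothesis and study goals in the protocol article, include "iii) to evaluate the efficacy in terms of improvement perceived by the patient with LBPGP at two weeks after starting treatment". The Variables section returns to this outcome: "At the end of treatment (T2), the patient’s perceived improvement will also be assessed". It then notes that "A 7-point Likert scale has been recommended to assess the perceived improvement of a patient with non-specific LBP", says that opinions differ on the categories, and adopts the version of a cited source. The question itself reads "How satisfied are you with the results of your recent treatment for low back pain and/or posterior pelvic pain".

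The favourable end of the answer scale is printed as "1 = very satisfied, 2 = very satisfied, 3 = somewhat satisfied". Code 4 is the neutral category. The unfavourable end is "5 = somewhat dissatisfied, 6 = very dissatisfied, and 7 = extremely dissatisfied".

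The Statistical analysis section places this outcome with the quantitative ones, "secondary outcomes (change at 2 weeks in functional status with respect to pain, quality of life, and improvement perceived by the patient". These are compared between VAAc and SOC as mean differences (t-test, or Mann-Whitney if not normal) and then by linear regression. The comparisons are repeated for VAAc against PAAc and NSAAc.

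**The concern.** The aim and the instrument name different things. The aim is about how much better the woman thinks her pain has become; the question is about how content she is with what treatment achieved. The two usually move together, but they can part. A woman with little change may be content because she expected little, and a woman who improved may be discontented because she hoped for more. The neutral point of the scale is indifference, which is not the same as no change. A difference between arms on this item would, as planned, be reported as a difference in perceived improvement.

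Separately, if the labels on the patient form are as printed, a woman who is very satisfied has two boxes with the same words. Her choice between codes 1 and 2 means nothing, yet it enters a mean or a rank as if it did.

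**Working it through.** **Aim against item.** The aim and the sentence introducing the item both speak of perceived improvement. The question does not ask whether the pain is better, unchanged or worse. No other item for this aim is described. The question is, however, tied to results and to the low back or pelvic pain, so it carries some information about improvement.

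**Label count, from the Variables section.**

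| Code | Label |
|---|---|
| 1 | very satisfied |
| 2 | very satisfied |
| 3 | somewhat satisfied |
| 4 | indifferent |
| 5 | somewhat dissatisfied |
| 6 | very dissatisfied |
| 7 | extremely dissatisfied |

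Distinct favourable answers: 2. Neutral: 1. Distinct unfavourable answers: 3. Total 2 + 1 + 3 = 6 for seven codes. Reflecting the lower half about code 4 gives *extremely satisfied* for code 1, which is the likely intention.

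**How much the duplicate could matter.** The documents give no answer distribution, so the following shares for codes 1 to 7 are assumptions for illustration only:

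- VAAc: 0.25, 0.30, 0.20, 0.10, 0.08, 0.05, 0.02
- SOC: 0.08, 0.17, 0.25, 0.20, 0.15, 0.10, 0.05

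Mean = Σ(share × code). The standardised difference is the difference in means divided by the square root of the average of the two variances.

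| Treatment of codes 1 and 2 | Mean VAAc | Mean SOC | Difference | SD | Standardised |
|---|---|---|---|---|---|
| Distinct labels | 2.69 | 3.67 | 0.98 | 1.571 | 0.624 |
| Random half split | 2.665 | 3.625 | 0.96 | 1.610 | 0.596 |
| All recorded as 1 | 2.39 | 3.50 | 1.11 | 1.770 | 0.627 |
| All recorded as 2 | 2.94 | 3.75 | 0.81 | 1.401 | 0.578 |

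The contrast moves from 0.62 to somewhere between 0.58 and 0.63. The favourable end is blurred, but the comparison survives. A random split gives each affected woman a score of 1.5 ± 0.5, which is noise and not by itself a bias between arms.

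**What is not affected.** The sample size rests on the primary outcome and reproduces: 2 × [25 × (2.576 + 1.282) / 20]² = 46.5, so 47 per group; 47 / 0.90 = 52.2, so 53; 4 × 53 = 212. Nothing in it depends on this item.

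**A related detail.** The Statistical analysis section compares these outcomes as differences between baseline and two weeks. The satisfaction item is described only at T2 and refers to treatment already received, so no baseline value for it is described.

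**The case against.** The strongest reply has four parts.

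First, the duplicate label is probably a slip in the article. The intended wording can be read off the other end of the scale, and the form that patients complete is not shown. This stands as an account of the likely cause, but the form still has to be checked.

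Second, the item was chosen deliberately from a cited source, and it asks about results of treatment for this pain. That also stands, and it is why the item counts as an imperfect proxy. It does not make satisfaction and improvement the same quantity.

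Third, pain and disability are measured directly by iVAS and the Roland-Morris questionnaire at T0 and T2. The outcome is named in the aims and in the Statistical analysis section but not in the opening list of outcomes under Variables. Its weight in the trial is therefore modest. This stands and limits the size of the point.

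Fourth, a reader might infer that the item must favour VAAc, because SOC women know that they received no ear treatment and have nothing to rate. The protocol does not support this. Standard obstetric care includes an explanation of the cause, self-care advice, training in stretching and a recommendation on paracetamol, so SOC women do have a treatment to rate. A global-change question would also be answered by unblinded SOC women, so replacing the item would not remove that influence. The repeated comparisons with PAAc and NSAAc are between arms whose patients are blinded. Bias in favour of VAAc over SOC is possible, but it can be neither shown nor sized from the document.

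**Conclusion.** The point holds in a limited form. As printed, aim iii is served by a satisfaction item that is only an imperfect proxy for perceived improvement, and its seven codes give six distinct answers.

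A reader might go further and conclude that the item cannot inform aim iii at all. That does not follow. The duplicate costs only the split between codes 1 and 2, and the question is anchored to treatment results for the pain in question.

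The size of the duplicate's effect rests on assumed answer shares; under them the loss is slight. The consequence of measuring satisfaction in place of improvement cannot be put in figures from the document. It lies in what may be concluded: a difference on this item is a difference in satisfaction with results. The effect is confined to one secondary outcome.

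**What to change.** 1. Check the T2 form. If code 1 carries the duplicated label, correct it to mirror code 7 (*extremely satisfied*); if the form is already right, correct the protocol text only.
2. If the duplicated wording was used, merge codes 1 and 2 for the women who answered it. An analysis that pools both versions of the form should use the merged coding throughout. State the value given to the merged category beforehand, since the illustration gives 0.627 or 0.578 according to that choice, or compare by ranks.
3. Report this item as satisfaction with treatment results.
4. Then either restate aim iii as satisfaction with results, or add one seven-point global-change item at T2 in all four arms, with symmetric labels from very much better through no change to very much worse, and analyse that as perceived improvement.
5. Describe the analysis of either item as a comparison between arms at T2.

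The cost is at most one added question and one corrected label. The trial is described as recruiting, so the form can still be changed. The downside is that women already assessed will have only the satisfaction item, so a global-change outcome would rest on fewer women. Restating the aim avoids that loss but gives up perceived improvement as a measured outcome.

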### Study scope and subjects

The study population will be composed of pregnant women (24 to 36 weeks’ gestation), aged 17 years or more, referred by their family physicians from the 21 primary care centres participating in the study, belonging to the Andalusian Public Health System and located in the provinces of Seville and Málaga, diagnosed with pregnancy-related LBPGP and who have not previously received auricular acupuncture. Women with LBPGP that began before the pregnancy, or presenting any of the ‘red flags’, which would require examination to rule out the possible presence of LBPGP secondary to inflammatory, infectious, traumatic, neoplastic, or degenerative processes, together with women receiving anticoagulant treatment or presenting dermatitis of the auricle, will be excluded from the study.

The women will be given the following information: “*This study is being conducted to compare the effects of standard obstetric care either alone or in conjunction with one of three types of stimulation of the ear (auricular acupuncture). One of these is similar to traditional Chinese auricular acupuncture, while the others do not follow these principles. One is a placebo intervention, but all have been associated with positive outcomes in various clinical studies*”. The women will also be informed of the potential risks associated with different types of auricular acupuncture (infection, pain at the puncture site, fainting, bruising) and that they may terminate their participation in the study at any time without any penalty or loss of the benefits to which they are entitled. All study participants must sign the informed consent form.

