### Randomisation and blinding procedures

The four study arms will be randomised centrally, at the Costa del Sol Hospital, Research Support Unit, to achieve a 1:1:1:1 allocation ratio, stratified by healthcare centre. The health professionals taking part in the study will not be involved in the randomisation process. Patients who meet the inclusion criteria and give their signed informed consent will be included in the study. After inclusion, the researcher will contact the randomisation centre, where the patient’s data will be recorded, and the midwife will be informed, by telephone and by fax, of the patient’s allocation to one of the four study arms. This procedure ensures that randomisation will not be influenced by any of the researchers involved. The patients assigned to the VAAc, NSAAc, and PAAc groups will be blinded with respect to the treatment allocated to them.

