#### Non-specific auricular acupuncture (NSAAc)

The needles used in the non-specific auricular acupuncture group will be the same as in the VAAc group, but they will be applied at auricular points that are non-specific for LBPGP, and which instead correspond to anatomic locations in the ankle, wrist, and shoulder (Figure 3).

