#### Placebo acupuncture (PAAc)

The devices used in the placebo group will be supplied by Seirin (Pyonex Placebo, Seirin, Shizuoka, Japan) and by 3B Scientific (Spain). They will be identical to those used in the VAAc group, but without the needle [34] (Figure 2), and will be applied at the same non-specific points as for the NSAAc group.

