## Discussion

When auricular acupuncture is practiced according to the principles of Traditional Chinese Medicine, it is an individualised treatment. In this study we have designed a semi-standardised treatment protocol that approximates standard clinical practice, which is sufficiently flexible and straightforward so that it can be performed by midwives without prior training, and which enables reproducibility.

As this experimental study is designed to be applied by medical personnel whose training is limited to an intensive 4-hour course in the technique, obviously the auricular acupuncture treatment cannot be performed to its full extent. For this reason, we have limited the number of points where acupuncture needles will be applied, and therefore the therapeutic effect obtained may be less than that otherwise to be expected. This limitation will produce an effect contrary to the study hypothesis.

Moreover, the patients assigned to the PAAc and NSAAc groups, due to the healthcare provided and the effects of dermatological stimulation, however minimal, may achieve some positive results. This effect, too, is contrary to the study hypothesis, but to a certain extent will reflect the non-specific effect of the intervention.

A double-blind study cannot be carried out because the therapist must know which treatment is being applied. We have attempted to minimise the consequences of this situation by ensuring that the professional who provides the treatment does not intervene in the assessment of the outcome. Furthermore, the blinding of the evaluators and the patients is designed to be highly effective. In addition, a question will be included to determine the patients’ perceptions regarding the type of auricular acupuncture received. Since the main outcome variable and many of the secondary ones will be recorded by means of a self-administered questionnaire no added bias will be caused by the intervention of the midwife in this area.

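### The blinding question assumes two auricular groups although three are blinded, so the right answer for NSAAc is undefined and blinding of VAAc versus NSAAc is checked only indirectly

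*Protocol article*

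**What the plan says.** All places are in the protocol article.

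- **Randomisation and blinding procedures:** "The patients assigned to the VAAc, NSAAc, and PAAc groups will be blinded with respect to the treatment allocated to them". That makes three blinded arms.
- **Study scope and subjects:** the information read to the women describes standard care alone or "in conjunction with one of three types of stimulation of the ear (auricular acupuncture". It says that one type resembles the traditional Chinese method, that the others do not, and that one is a placebo. It does not mention needles or ear points.
- **Non-specific auricular acupuncture (NSAAc):** on the device, the section says "The needles used in the non-specific auricular acupuncture group will be the same as in the VAAc group". Only the placement differs: the chosen ear points are not those meant for this pain.
- **Placebo acupuncture (PAAc):** devices "identical to those used in the VAAc group, but without the needle", placed at the NSAAc points.
- **Variables:** once treatment is over, allocation to "one of the two auricular acupuncture groups (real or placebo) will be verified by the following dichotomous question". The question reads "Do you think you were assigned to the real auricular acupuncture group or to the placebo group".
- **Discussion:** the therapist cannot be blinded, but "Furthermore, the blinding of the evaluators and the patients is designed to be highly effective", and the question is cited as the means of learning which type of acupuncture women believed they had.

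**The concern.** The question has two answers and the blinded part of the design has three arms. *Real* fits VAAc and *placebo* fits PAAc. NSAAc sits between them, because it shares the needle with VAAc and the ear points with PAAc.

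The NSAAc arm exists for the specificity question. The secondary hypothesis is that VAAc does better than both NSAAc and PAAc. One aim is to separate placebo, specific and non-specific effects, and the Statistical analysis section repeats the analyses for both contrasts. The outcome is self-reported pain and the therapist knows the allocation, so patient blinding is the main protection for these contrasts. For VAAc versus NSAAc, the blinding that matters is blinding to where the needle is placed, and the response options do not ask about that.

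The question's wording decides what is collected. An analysis plan can add a scoring rule later, but it cannot recover a distinction that the women were never offered.

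**Working it through.** **1. Arm sizes (Sample size section).** Inputs: difference 20 mm, SD 25 mm, alpha 0.01 two-sided, beta 0.10, 10% loss.

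- n per group = 2 × 25² × (2.576 + 1.282)² / 20² ≈ 46.5, rounded up to 47.
- 47 / (1 − 0.10) = 52.2, rounded up to 53; 4 × 53 = 212.

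The plan's 47, 53 and 212 are all reproduced. The blinded arms total 3 × 53 = 159 women, of whom NSAAc makes up 53, or one third.

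**2. Does each arm have a defined correct answer?**

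| Arm | Device | Ear points | As described to the women | Correct answer |
|---|---|---|---|---|
| VAAc | needle | specific | the traditional type | *real* |
| NSAAc | needle | non-specific | neither traditional nor placebo | not defined |
| PAAc | no needle | non-specific | the placebo | *placebo* |

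For NSAAc, *real* can be defended because she has needles and only one type is called a placebo. *Placebo* can be defended because only one type follows the traditional principles. The article gives no rule for choosing between them.

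**3. What the missing rule does to a blinding index.** Assume that blinding is perfect, so that the same share q answers *real* in every auricular arm. A Bang-type index is the share correct minus the share incorrect. For NSAAc it is 2q − 1 if *real* is scored correct, and 1 − 2q if *placebo* is. The values of q are assumptions.

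| q | NSAAc index, *real* correct | NSAAc index, *placebo* correct |
|---|---|---|
| 0.50 | 0 | 0 |
| 0.67 | +0.34 | −0.34 |
| 0.80 | +0.60 | −0.60 |

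Unless answers split evenly, the sign of the index depends on a rule that the article does not give.

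**4. What can still be checked.** The share answering *real* can be compared between VAAc and NSAAc without any scoring rule. With 47 per arm (the number left after the planned loss), two-sided alpha 0.05, a normal approximation with pooled variance under the null, and assumed shares, the power is:

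- 80% versus 50%: about 87%
- 80% versus 60%: about 56%
- 80% versus 70%: about 20%

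A large difference would probably be detected, but a moderate one could easily be missed. Similar shares would not settle the matter either. A woman who recognises that she has needles at non-specific points may still answer *real*.

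**The case against.** The strongest reply is that the check is imperfect but still works. The women are told that only one of the three types is a placebo, and NSAAc uses the same needles as VAAc, so *real* is a reasonable correct answer for NSAAc. On that view only a scoring rule is missing. The shares answering *real* can be compared between arms in any case. The credibility scale adds evidence: its first two items are asked after the first session, before the 2-week outcome, and credibility is described by group. The check is also ancillary, since no planned test depends on it.

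Much of this stands. A reader might infer that NSAAc women have no correct answer at all, or that blinding of VAAc versus NSAAc cannot be verified. The documents support neither. The answer is undefined rather than non-existent, and an indirect comparison remains.

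A reader might also infer that a question asked after treatment will show false unblinding if the treatment works. That is possible in principle, but its size would rest on an assumed rule linking pain relief to the answer given, and the article offers no such rule. It also bears more on VAAc versus PAAc than on NSAAc.

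The reply does not remove the mismatch between two groups and three. Nor does it show that two options can reveal whether women were blind to point location. Credibility measures how convincing a treatment seemed, which is different from what a woman thinks she was given.

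**Conclusion.** The point holds in a limited form. The blinding check is written for two auricular groups in a trial that blinds three. For 53 of 159 planned blinded women the correct answer is undefined, so a correct-guess assessment cannot be scored for NSAAc, and blinding of VAAc versus NSAAc is tested only through the shares answering *real*. This follows from the text and the planned arm sizes alone. The index values and powers rest on assumed response shares and serve only to illustrate.

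The consequence is confined to how well the specificity comparisons can be defended. The primary VAAc versus SOC comparison is untouched, because SOC is not blinded, and so is the sample size. The change is worth making now: recruitment is under way, and each woman who passes T2 leaves only a two-option answer.

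**What to change.** 1. In the Variables section, change two auricular groups to three.
2. Keep the question at T2, but place it after the T2 outcome measures are completed, so that it cannot influence them.
3. Offer four answers in the terms of the information already given to the women: the type resembling traditional Chinese ear acupuncture; a type not based on those principles but not the placebo; the placebo; don't know. Each of the first three then matches one arm.
4. Tabulate the answers separately for VAAc, NSAAc and PAAc.
5. State, before any answers are examined by arm, how two-option answers already collected from NSAAc women will be scored.

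Two alternatives are best avoided. Options that mention a missing needle or different ear points would disclose design details that the women have not been told. Moving the question to T1 would draw attention to allocation before the self-reported primary outcome, and it would not make the answer independent of response, because pain is already measured at T1.

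The cost is one changed form item and one table. Women already past T2 will have only the old answer, so the two versions need to be reported separately. A T2 answer may still partly reflect how the woman's pain responded, so it should be read alongside the early credibility items.
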